**Figure 2 F2:**
[figure not shown]
Timeline of events for research participant. ABPM, ambulatory blood pressure monitoring; GP, general practitioner; HBPM, home blood pressure monitoring.

### Data analysis

#### Objective 1: to identify which BP will be used to calculate the rate of persistent hypertension at 12 weeks postpartum

The first and second BP readings will be compared with the third reading to assess if they vary by >10/5 mm Hg. The mean or median of all BPs will be used if no significance is found or the third BP reading will be used for interpretation if there is a significant difference (>10/5 mm Hg) between BPs. The BP taken at three time periods (morning, midday and evening) will also be analysed to assess if findings vary significantly by >10/5 mm Hg. If no significance is found, the mean or median BP readings for the day will be calculated and used for further analysis. If significant difference found, each time period will be compared with daytime ABPM to see which time point mostly correlates with daytime ABPM. This will be analysed using one sample t-test of the difference and intraclass correlation co-efficient (ICC).

Using descriptive statistics, HBPM readings for participants (not taking antihypertensive medication) will be categorised as per European Society of Cardiology guidelines^21^ into:

Prehypertensive (BP ≥130–134/80–84 mm Hg)Hypertensive (BP ≥135–139/85–89 mm Hg)Normotensive (BP <130/80 mm Hg)

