The gold standard for diagnosing hypertension is 24-hour ambulatory blood pressure monitoring (ABPM).^11^ However, home blood pressure monitoring (HBPM) is becoming more widely used in maternity care, particularly in the antenatal period since the COVID-19 pandemic^12^ and more recently, self-management of BP in the postpartum period has been considered.^13^ To add to this expanding evidence-base, this study will assess the accuracy of HBPM versus ABPM and if there is a role for HBPM in the postnatal period for diagnosing hypertension.

This study will highlight the proportion of women with persistent hypertension from week 2 to 12 postpartum and whether these women share common characteristics such as raised body mass index and/or maternal age. This is valuable information for clinicians so they know which women are at higher of risk of uncontrolled hypertension and require closer blood pressure (BP) surveillance. The current national guidance for monitoring BP in the postpartum period is minimal and this research will therefore ascertain if the national guidance for monitoring hypertension^14^ in the postpartum period is sufficient. It will highlight if women who had HDP need further monitoring of hypertension between week 2 and week 8 postpartum and therefore highlight the important timelines for monitoring BP and the need for therapeutic intervention to control BP.

This study will ascertain if the HCPs involved in the care of women who may at be at increased risk of CVD due to developing HDP are educated about the risks and approaches to monitor for CVD. Roth *et al* undertook a systematic review assessing knowledge gaps of women and HCPs around CVD risk and HDP.^15^ The authors concluded that there was a low level of knowledge among women and HCPs concerning CVD risk and HDP. If HCPs and women are not educated about the risks, the path to significant heart disease is expedited. The postnatal period presents an optimum time for women to be receptive to change and lifestyle modifications,^16^ with opportunities for HCPs to influence positive change.

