The main objective of this prospective cohort study is to observe the recovery (or lack thereof) of maternal hypertension from week 2 to week 12 after a pregnancy affected by new onset of hypertension and identify the prevalence of persistent postpartum hypertension in this cohort of women. A secondary objective will be to assess the accuracy of HBPM in comparison with ABPM to inform if HBPM can be used as an alternative method for diagnosing hypertension in the postpartum period. Other outcomes of interest will include women’s self-reporting of their 6-week to 8-week GP postnatal review, their perceived risk of developing CVD associated with HDP, their emotional well-being and their views on HBPM and ABPM. These objectives will be assessed via online questionnaires distributed at 8 and 12 weeks post partum, respectively. In addition, healthcare professionals involved in the postnatal care of women with HDP will receive an online questionnaire assessing their knowledge on HDP and associated CVD risk.

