### Sample size

To obtain an accurate estimate of persistent hypertension rate after birth, a sample size of 263 women with a history of HDP are required. The target sample size is 300 women to compensate for study withdrawal and incomplete BP data. This is based on the anticipated rate of persistent postpartum hypertension of approximately 20% and the corresponding width of 95% CI to be 10% as desired level of precision, with 80% probability of achieving such precision. Considerations were also given to the sample size required to assess agreement between HBPM and ABPM.

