### Data collection

#### Home blood pressure monitoring

Research participants will undergo HBPM every fortnight from week 2 post birth until week 12 as per a HBPM protocol based on that used by Alemida *et al*. Women will take three BP readings in the morning, early afternoon and in the evening, a total of nine BP readings per day, for three consecutive days.^17^ At week 12, women will undergo 24-hour ABPM (figure 1).

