#### Objective 3: to assess the rate of hypertension over the postpartum period (weeks 2–12)

Using descriptive statistics, hypertension rates will be categorised under normotensive (<130/80 mm Hg), prehypertensive (130–135/80–85 mm Hg) or hypertensive (>135/85 mm Hg) at 2-week intervals post birth until 12 weeks postpartum. Univariate and multivariable logistic regression will be used to study what variables are associated with persistent postpartum hypertension at 12 weeks postpartum.

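### The 12-week persistent-hypertension rate is defined from home readings only, although ABPM, the protocol's own gold standard, is planned for all women at week 12

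*Protocol article*

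**What the plan says.** The main objective, at the end of the Introduction, has two parts: to follow the recovery of blood pressure from week 2 to week 12, and to "identify the prevalence of persistent postpartum hypertension in this cohort of women". The Sample size section rests on that prevalence: an "anticipated rate of persistent postpartum hypertension of approximately 20" per cent, "the corresponding width of 95% CI to be 10% as desired level of precision", "with 80% probability of achieving such precision", which leads to 263 women required and 300 targeted.

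On measurement, the Introduction says "The gold standard for diagnosing hypertension is 24-hour ambulatory blood pressure monitoring (ABPM", and the Data collection section says "At week 12, women will undergo 24-hour ABPM". Home monitoring runs every fortnight from week 2 to week 12, so both methods are due at week 12.

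The Data analysis section assigns the roles:

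- **Objective 1** is "to identify which BP will be used to calculate the rate of persistent hypertension at 12 weeks postpartum". Its options are the third home reading, a mean or median of home readings, or one home time of day. ABPM enters only if the times of day differ, and then as the yardstick for choosing among them. The values finally categorised are named as home readings.
- **Objective 2** takes HBPM as the test under evaluation and ABPM as the reference. Sensitivity, specificity and predictive values are to be estimated, and the HBPM threshold may be moved to find the best one.
- **Objective 3** classifies women "at 2-week intervals post birth until 12 weeks postpartum" and then models persistent hypertension at 12 weeks by logistic regression. It does not say which instrument defines that outcome.

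**The concern.** The study will hold a reference-standard result for most women at the time point of its main prevalence estimate, yet the rule for that estimate considers only the test being evaluated. Any false positives and false negatives of HBPM then pass straight into the prevalence. If Objective 3 uses the same status, as its continuation of the fortnightly series suggests, they pass into the risk-factor analysis too.

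At stake are the location of the prevalence estimate, which the sample size treats as free of measurement error, and the size of the associations with severity, age, BMI and ethnicity. The paper could also headline an HBPM prevalence while its own Objective 2 shows how often HBPM disagrees with the gold standard.

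**Working it through.** **Inputs from the article:** anticipated rate p = 0.20; 95% CI with full width 0.10, so half-width 0.05; 80% assurance; n = 263 required and 300 targeted. **Not in the article:** HBPM sensitivity (Se) and specificity (Sp) against ABPM. These are assumed below over a range.

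**1. The plan's own figure.** Take the smallest n for which the 95% CI width is at most 0.10 with probability at least 0.80, with X ~ Binomial(n, 0.20). The Wilson interval gives n = 263 (probability 0.819 at that n) and the Wald interval gives 264. The stated 263 reproduces. The calculation uses only the rate, the width and the assurance, so it has no allowance for misclassification and does not change if the rate is taken from ABPM.

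**2. Effect on the prevalence.** With ABPM as the truth, apparent rate = Se × 0.20 + (1 − Sp) × 0.80, and the share of labelled cases that are true is Se × 0.20 / apparent rate.

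| Assumed Se / Sp | Apparent rate | Shift | True among labelled cases |
|---|---|---|---|
| 0.70 / 0.95 | 0.14 + 0.04 = 18% | −2 points | 0.14/0.18 = 78% |
| 0.80 / 0.95 | 0.16 + 0.04 = 20% | 0 | 0.16/0.20 = 80% |
| 0.85 / 0.90 | 0.17 + 0.08 = 25% | +5 points | 0.17/0.25 = 68% |
| 0.90 / 0.85 | 0.18 + 0.12 = 30% | +10 points | 0.18/0.30 = 60% |

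The shift is zero only where 0.20 × (1 − Se) = 0.80 × (1 − Sp). At n = 263 the 95% Wald interval covers the true 20% in 94% of samples without error. With HBPM it does so in 82% at 0.70/0.95, 69% at 0.80/0.90 (apparent rate 0.16 + 0.08 = 24%) and 5% at 0.90/0.85.

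**3. Effect on an odds ratio, if the regression uses HBPM status.** Assume half the women are exposed, an overall rate of 20% and a true odds ratio of 2.0. The true risks are then 0.2543 and 0.1457. With Se/Sp 0.85/0.90 that do not depend on exposure, the apparent risk is 0.10 + 0.75 × risk:

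- exposed: 0.10 + 0.75 × 0.2543 = 0.2907
- unexposed: 0.10 + 0.75 × 0.1457 = 0.2093
- apparent odds ratio: (0.2907/0.7093) / (0.2093/0.7907) = 1.55

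At 0.90/0.95 the same steps give about 1.72.

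**4. Room for missing ABPM.** The target allows a loss of 1 − 263/300 = 12.3%. As an illustration, a 20% loss leaves 240 women and an expected full width of 2 × 1.96 × √(0.20 × 0.80/240) = 0.101, just over the planned 0.10.

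**The case against.** The strongest counter-argument is that HBPM at week 12 is a defensible choice. It is the only measure at weeks 2 to 10, and the main objective includes the course of recovery. Switching instruments at the last point would mix recovery with a change of method. That is a good reason to keep HBPM for the series, week 12 included. It is no reason to base the stand-alone 12-week prevalence on it, since both rates can be reported side by side.

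The other objections limit what can be claimed, and they stand:

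- A reader might infer that the ABPM diagnosis goes unused. It does not: Objective 2 uses it for kappa, predictive values and McNemar's test, which compares the two paired rates. The ABPM-defined rate will be visible in that cross-tabulation. It is simply not the one designated for the main prevalence.
- A reader might take it as stated that the regression outcome is home-based. Objective 3 names no instrument, so this is an inference from Objective 1.
- A reader might assume that every woman will have an ABPM result. It is planned for all, but the article expects withdrawal and incomplete BP data.
- The accuracy values are all assumed, and the article does not say which instrument the anticipated 20% reflects.

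**Conclusion.** The point holds as a worthwhile and inexpensive improvement. Objective 1 states a rule that draws the 12-week rate from home readings only, so this is a stated choice and not a detail left to a fuller document. It sits poorly beside the article's own ranking of ABPM and its own uncertainty about HBPM.

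The size is conditional. With ABPM as truth, a true rate of 20% and the assumed accuracy range, the apparent rate runs from 18% to 30%, so the shift can equal or exceed the planned half-width of 5 points. Two stronger readings are not supported. The documents do not show that the prevalence will be overstated: the direction is unknown, and errors can cancel in the total, as at 0.80/0.95, although one labelled case in five is then still false. Nor do they show that associations must shrink: the fall from 2.0 to about 1.55 needs error unrelated to the covariate, and differential error could bias either way. The sample size itself is sound for a rate measured without error.

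**What to change.** Reword Objectives 1 and 3 so that persistent hypertension at 12 weeks, for both the prevalence and the logistic regression, is defined by the week-12 daytime ABPM result at one prespecified threshold. Daytime is the natural index because Objectives 1 and 2 already use it as the comparator. Keep HBPM for the weeks 2–12 course and report the week-12 HBPM rate beside the ABPM rate. Add a sensitivity analysis that uses the week-12 HBPM result where ABPM is missing.

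No new measurement is needed and the required 263 is unchanged. The cost is that women without a valid ABPM leave the primary estimate. If withdrawal plus missing ABPM exceeds about 12% of 300, the estimate rests on fewer than 263 women and the achieved precision must be restated.

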#### Objective 2: to compare the accuracy of HBPM against ABPM (gold standard) at 12 weeks postpartum

Cohen’s kappa will be used to measure the agreement between HBPM and day ABPM in diagnosing hypertension phenotypes. HBPM will also be compared with night and 24 hours ABPM indices. Accuracy of HBPM will be assessed through sensitivity, specificity, positive and negative predictive values. HBPM will be compared with night and 24 hours ABPM indices to assess. Thresholds for diagnosing hypertension in HBPM will be adjusted to explore the optimal threshold using area under the receiver operating characteristic curve or kappa score. The McNemar’s test will be used to assess whether there is a systematic difference between the HBPM and ABPM for diagnosing hypertension. ICC will be used to check for agreement and Bland-Altman diagrams will also be used to check for random/systematic effects between HBPM and ABPM measurements.

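### Objective 1 lets the study data choose the home BP value behind the primary 12-week rate, by a trigger whose level is not fixed; one all-readings summary should be set in advance

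*Protocol article*

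**What the plan says.** The Data analysis section of the protocol article heads its first objective "to identify which BP will be used to calculate the rate of persistent hypertension at 12 weeks postpartum". Three choices follow, all made on the study's own readings.

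- **Reading order.** "The first and second BP readings will be compared with the third reading to assess if they vary by >10/5 mm Hg". Then: "The mean or median of all BPs will be used if no significance is found"; otherwise "the third BP reading will be used for interpretation if there is a significant difference (>10/5 mm Hg) between BPs".
- **Mean or median.** Both are named for the no-difference case, and neither is chosen.
- **Time of day.** Morning, midday and evening values are checked against the same limit. If they differ, "each time period will be compared with daytime ABPM to see which time point mostly correlates with daytime ABPM", using a one-sample t-test of the difference and the ICC.

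Under Objective 2, "Cohen’s kappa will be used to measure the agreement between HBPM and day ABPM in diagnosing hypertension phenotypes" and "Accuracy of HBPM will be assessed through sensitivity, specificity, positive and negative predictive values"; ICC and Bland-Altman plots are added. No separate sample is described for selecting the period and for evaluating it. The Home blood pressure monitoring section sets three readings at each of three times on three consecutive days, and ABPM at week 12.

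**The concern.** The prevalence of persistent hypertension belongs to the main objective, and the sample size is built on it. The definition of the BP value that makes a woman hypertensive should therefore not depend on how the readings turn out. Three problems follow from the text as it stands.

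1. The trigger is worded both as significance and as a fixed 10/5 mm Hg limit, as if these were one criterion. Neither the level of application nor the way the systolic and diastolic limits combine is given. Two analysts could follow the text faithfully and obtain different estimators.
2. When triggered, each rule drops two-thirds of the readings that the women were asked to take.
3. In the time-of-day branch, the HBPM period would be picked by its agreement with daytime ABPM and then scored for agreement with daytime ABPM in the same women.

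**Working it through.** **The plan's own figure.** Inputs from the Sample size section: rate 20%, 95% CI width 10%, 80% probability of achieving it. The Wilson width is 2z/(1+z²/n) × √(p(1−p)/n + z²/4n²). Summing binomial probabilities at p = 0.20 over outcomes with width ≤ 0.10 gives 0.819 at n = 263, the smallest n that reaches 0.80. So 263 reproduces, and the planned half-width is 5 percentage points. The point raised here does not alter it.

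**Readings kept.**
- Full episode: 3 readings × 3 times × 3 days = 27.
- Third reading only: 1 × 3 × 3 = 9.
- One time of day only: 3 × 1 × 3 = 9.
- Both rules: 1 × 1 × 3 = 3.

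**How often noise alone triggers the limit.** The documents give no BP SDs, so within-sitting SDs of 3/2 to 8/5 mm Hg (systolic/diastolic) are assumed, with independent normal errors and no true difference between readings. A difference of two readings has SD s√2. For a single pair:
- SD 3/2: P(systolic difference > 10) = 2[1 − Φ(10/4.24)] = 0.018; P(diastolic difference > 5) = 2[1 − Φ(5/2.83)] = 0.077.
- SD 8/5: 2[1 − Φ(10/11.31)] = 0.377; 2[1 − Φ(5/7.07)] = 0.480.

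The rule compares two pairs (first with third, second with third) that share the third reading, so the combined probability was simulated:

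| Level at which the rule is applied | SD 3/2 | SD 8/5 |
|---|---|---|
| Per sitting, either limit exceeded | 17% | 87% |
| Per sitting, both limits exceeded | 0.5% | 41% |
| Each woman's means over 9 sittings (SD divided by √9 = 3), either limit | 0% | 8% |
| Cohort mean, n = 263 | not from noise | not from noise |

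For the last row, the SE of the mean difference from one sitting per woman is s√(2/263). That is 0.26/0.17 mm Hg at SD 3/2 and 0.70/0.44 at SD 8/5. A mean difference of 10/5 lies more than 11 SEs from zero even in the noisier case (5/0.44 = 11.4). If systolic and diastolic errors correlate at 0.5, the per-sitting either-limit range is 16-85%, much the same.

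**Significance against 10/5.** At n = 263 with an assumed SD of differences of 5 to 10 mm Hg, a t-test declares a mean difference of 1.96 × 5/√263 = 0.6 to 1.96 × 10/√263 = 1.2 mm Hg significant. The two wordings of the trigger are therefore roughly an order of magnitude apart for systolic BP. The bracketed limit in the third-reading sentence favours the 10/5 meaning.

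**Selecting the period on ABPM.** Simulation with three equivalent periods, n = 263, between-woman SD 11, woman-by-period SD 5 or 7, reading SD 5 or 6 and ABPM error SD 4 or 5 (all assumed):

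| Scenario | ICC, period fixed in advance | ICC, best period chosen on the same women | ICC, mean of all |
|---|---|---|---|
| Lower noise | 0.846 | 0.856 | 0.905 |
| Higher noise | 0.755 | 0.771 | 0.849 |

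Selection optimism is 0.856 − 0.846 = 0.010 to 0.771 − 0.755 = 0.016 in ICC. For kappa it is 0.610 − 0.597 = 0.013 to 0.514 − 0.497 = 0.017. The chosen period falls below the all-readings mean by 0.905 − 0.856 = 0.049 to 0.849 − 0.771 = 0.078 in ICC. With a woman-by-period SD of 4 the gap is 0.915 − 0.882 = 0.033.

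**The case against.** **The rule may be a cohort-level one.** The objective's heading poses one study-wide question, and the t-test and ICC are cohort statistics. Read so, noise does not fire a 10/5 limit. This stands. A reader might infer that noise alone sets off the rule in most women; that needs application per sitting, chiefly with either limit counting, and the text fixes neither.

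**The article is condensed.** The level of application and the and/or question may be settled in the full protocol or analysis plan. That is fair. What does not depend on them is the stated design: the value is chosen after looking at the data, among several candidates.

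**The primary rate need not be biased by the rule.** A reader might infer that the third-reading rule distorts the rate. Under an assumed systolic pattern of 3/1.5/0 mm Hg across the sitting, one simulation moves it from 20.6% (mean) to 18.2% (rule). But the shift comes from the assumed fall. With no fall the rate moves by at most about 0.3 points. With this same fall the third reading is the unbiased one: a second simulation gives a true rate of 19.2%, 21.2% by the mean and 19.8% by the rule. The documents do not support a claim of bias from the rule.

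**Circularity is narrow.** It belongs only to the time-of-day branch, which needs a difference above 10/5 to open; the third-reading rule never uses ABPM. That the best-matching period then becomes the HBPM value is implied by the heading and not stated. A reader might expect materially inflated accuracy in Objective 2. At n = 263 the inflation is about 0.01-0.02, and the chosen period still agrees less well with ABPM than the mean of all readings.

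**The t-test.** One might object that a noisy period passes a t-test more easily. The ICC is used alongside it and would count against a noisy period, so little rests on this.

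**Conclusion.** The concern holds in a limited form. Objective 1 leaves the HBPM value behind the primary 12-week rate to the data, through a trigger that can be read in ways giving anything from no noise-driven switching to switching in about 87% of sittings. The certain cost, whenever a rule fires, is the loss of 18 of 27 readings, or 24 of 27 if both fire. The reuse of daytime ABPM is a real but small flaw, confined to one conditional branch; losing readings there matters more (about 0.03-0.08 in ICC). The reading counts follow from the protocol. The trigger rates and ICC figures rest on assumed SDs. The sample size is unaffected. This should be corrected, but it does not by itself invalidate the primary estimate.

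**What to change.** State in advance one HBPM summary for every woman and every fortnightly episode: the mean of all valid readings in the 3-day session (up to 27). Use it for the primary 12-week rate, for the rates over weeks 2-12 and for the comparison with ABPM in Objective 2. Keep the third-reading and single-time-of-day values as sensitivity analyses, each reported with its Bland-Altman mean difference and limits of agreement against daytime ABPM. If the 10/5 check is retained as a description, say at which level it applies and how the two limits combine, and drop the word significance for it.

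The cost is analysis wording only: no extra data, visits or participants. The one downside is that, if BP falls across a sitting, the all-readings mean will be slightly higher than the third reading. The sensitivity analysis would show by how much.

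### Objective 1 classifies blood pressure only in untreated women and Objective 3 by blood pressure alone; neither rule matches the whole-cohort prevalence, and both probably understate it

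*Protocol article*

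**What the plan says.** Three places in the protocol article bear on who is counted.

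- **Introduction, main objective.** The study is to "identify the prevalence of persistent postpartum hypertension in this cohort of women". The cohort is women with new-onset hypertension in pregnancy or shortly after birth. The eligibility section sets no condition on medication.
- **Data analysis, Objective 1.** The heading gives its purpose as "to identify which BP will be used to calculate the rate of persistent hypertension at 12 weeks postpartum". Under it, "HBPM readings for participants (not taking antihypertensive medication) will be categorised" into normotensive, prehypertensive and hypertensive. The section does not say what happens to readings from women who are taking medication.
- **Data analysis, Objective 3.** At each two-week interval, "hypertension rates will be categorised under normotensive (<130/80 mm Hg), prehypertensive (130–135/80–85 mm Hg) or hypertensive (>135/85 mm Hg" mm Hg). There is no medication restriction and no rule for treated women. The same section uses logistic regression to study "what variables are associated with persistent postpartum hypertension at 12 weeks postpartum".

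The Sample size section says that "a sample size of 263 women with a history of HDP are required". It assumes a rate of about 20% and a 95% confidence interval 10 points wide, with 80% probability of achieving that width. The target of 300 allows for withdrawal and incomplete BP data.

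**The concern.** The article states two rules for one quantity, and neither delivers the prevalence named in the main objective.

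- **Objective 1 rule.** A woman on antihypertensives at week 12 is in neither numerator nor denominator. The result is a rate among untreated women, not among the cohort.
- **Objective 3 rule.** She is in the denominator and is judged on her measured BP. If treatment controls it, she counts as normotensive (or at most prehypertensive), the same as a woman who has recovered. If her BP is raised despite treatment, she counts as hypertensive.

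The women affected are those whose hypertension was judged to need drugs. The Introduction says the study should inform when drug treatment is needed, so setting these women aside, or counting them as recovered, works against that purpose. Where the rules are applied, the fortnightly rates and the regression outcome are affected too. Under the Objective 1 rule, the denominator would also change as women start or stop treatment, so the recovery curve would mix recovery with changes in who is counted. The Abstract names severity of the pregnancy disorder as a factor for the regression. If severe cases are treated more often, its association with persistence could be weakened.

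**Working it through.** **1. The plan's own figure.** Inputs from Sample size: rate 0.20, 95% interval, width 0.10, probability 0.80. With X ~ Binomial(n, 0.20), find the smallest n at which the interval width is at most 0.10 with probability at least 0.80. The Wilson interval gives n = 263 (probability 0.819), an exact match; the Wald interval gives 264. The sample size is therefore not in question. The planned half-width is 10/2 = 5 points.

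**2. Notation.** P is the share of the whole cohort with hypertensive-range BP or on treatment at week 12. t is the share of the whole cohort on treatment. c is the share of treated women whose BP is controlled. The document gives neither t nor c, so both are assumptions. P = 0.20 is taken from Sample size, which does not say how treated women are counted in that figure.

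**3. Formulas.**

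- Objective 1 rule: rate = (P − t)/(1 − t). The shift is P − (P − t)/(1 − t) = t(1 − P)/(1 − t), which is positive for every t > 0 and P < 1.
- Objective 3 rule: rate = P − t·c.

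**4. Results with P = 0.20.**

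| Treated share t (assumed) | Untreated-only rate | Shift, points | BP-only rate if c = 0.5 | Women classified under the Objective 1 rule, of 263 |
|---|---|---|---|---|
| 2% | 0.18/0.98 = 18.4% | 1.6 | 19.0% | 258 |
| 5% | 0.15/0.95 = 15.8% | 4.2 | 17.5% | 250 |
| 10% | 0.10/0.90 = 11.1% | 8.9 | 15.0% | 237 |
| 15% | 0.05/0.85 = 5.9% | 14.1 | 12.5% | 224 |

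At t = 10%, letting c run from 0.3 to 0.7 moves the BP-only rate from 17% to 13%.

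**5. Where the shift passes the half-width.** Set (0.20 − t)/(1 − t) = 0.15. Then 0.05 = 0.85t, so t = 5.9%. Under the BP-only rule with c = 0.5, the shift reaches 5 points at t = 0.05/0.5 = 10%.

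**6. If the 20% is instead the rate in untreated women.** The rate counting treated women as cases is 0.20(1 − t) + t, which is 21.6%, 24%, 28% or 32% for the same four values of t.

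**7. If not every treated woman is truly persistent.** Let q be the share of treated women who are, and let P now be the true cohort prevalence. The untreated rate is (P − tq)/(1 − t), which is below P whenever q > P. For example, with P = 0.20, t = 10% and q = 0.5, it is (0.20 − 0.05)/0.90 = 16.7%. The direction therefore needs only that treated women are persistently hypertensive more often than the cohort as a whole; the size depends on q.

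**The case against.** The strongest reply is that the parenthesis in Objective 1 may limit only one descriptive table. Objective 3 is the section headed as giving the rate over time, and it carries no restriction. This is a condensed article, and treated women may be handled separately in a fuller plan. That is possible, and it is why a downward bias is the consequence of following the text and not a certainty. It does not remove the point. The restriction is written under the heading that concerns the 12-week rate, it conflicts with the main objective, and reading Objective 3 instead still counts controlled treated women as non-cases. This is a conflict between stated rules, not a detail left for later.

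A reader might also infer more than the document supports:

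- **That treated women are persistent cases by definition.** The article does not define persistence by treatment. A woman whose drugs have not yet been withdrawn may have recovered, so counting treatment as a case is an analysis choice that needs to be stated.
- **That treated women never count under either rule.** Under Objective 3, a treated woman with raised BP is a case.
- **That the study loses its planned precision.** A lower rate narrows the interval. At t = 10% (11.1% of 237), the Wald width is 2 × 1.96 × √(0.111 × 0.889/237) = 0.080, inside the planned 0.10. The target also exceeds the requirement by 300 − 263 = 37 women. The harm is bias, not width.
- **That the bias is known to be large.** At 2% treated, the untreated-only shift is 1.6 points, well inside the half-width.

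**Conclusion.** The point holds as an inconsistency with a likely direction and an unknown size. Objective 1 and Objective 3 classify different sets of women, and neither estimates the whole-cohort prevalence in the main objective once treated women are to be counted as persistent. On the assumption that treated women are more often persistently hypertensive than untreated women, the 12-week rate is too low. The fortnightly rates and the logistic outcome are affected in the same way where these rules are applied. With 20% having raised BP or on treatment, the untreated-only rate ranges from 18.4% to 5.9% as the assumed treated share goes from 2% to 15%. Above about 6% treated, the shift is larger than the uncertainty the study was sized to allow. Because this decides the headline estimate, it should be settled before analysis.

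**What to change.** Reconcile Objectives 1 and 3 and state one classification for the 12-week rate, every fortnightly rate and the logistic outcome. A woman counts as hypertensive at an assessment if her BP is in the hypertensive range or she is taking antihypertensive medication at that assessment. The denominator is all women with data at that assessment. Report the untreated-only rate and the BP-only rate as sensitivity analyses, with the number of treated women at each time point.

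The cost is mainly wording. Applying the Objective 1 restriction already requires medication status, but the new rule needs it at each fortnightly assessment. The article's data collection sections do not mention recording it, so its availability should be confirmed. The downside is that some women still on treatment they may no longer need will count as cases; the two sensitivity analyses show how much this matters. The change is confined to how outcomes are classified and leaves clinical management as it is.
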